## Methods

### Study Design

This protocol describes a multicenter prospective cohort study that aims to evaluate the ability of the preemie test device to estimate GA of low-birth-weight newborns. A nested case–control study will evaluate the relationship between the optical properties of the skin and newborn respiratory complications related to prematurity.

### Study Settings, Ethics, and Dissemination

The study will be performed in the following hospitals: Hospital das Clínicas, Universidade Federal de Minas Gerais, and Hospital Sofia Feldman in Brazil; and in the Hospital Central de Maputo and Eduardo Mondlane University in Mozambique, all of which are referral centers for high-risk pregnancies and neonatal care. The University Research Council in Brazil acts as the coordinating center of this multicenter cooperation. Each local ethics review board will independently approve the study protocol. The ethical approval number is CAAE 91134218.4.0000.5149 in Brazil, and IRB00002657 in Mozambique. Parents will be asked to sign an informed consent form on behalf of the newborns as recommended by the Regulatory Bodies for Good Clinical Research Practice. The parents will retain the right to discontinue study participation at all times. The protocol of this clinical study is registered in the International Clinical Trials Registry Platform (RBR-33rnjf).

### Data Sharing Statement

The authors intend to share the minimal anonymized data set necessary to replicate the study findings. Unidentified data and study-related documents will be accessible online to the researchers and regulatory agencies. The corresponding author will provide data access under reasonable request.

### Patient and Public Involvement

A flyer with information on the relevance, aims, and procedures of this investigation will be distributed to parents of the newborns. Results will be disseminated through scientific publications, congress participation, and on the project website (http://skinage.medicina.ufmg.br). All participants will be volunteers and will not receive any compensation or advantages.

### Eligibility Criteria and Participant Timeline

A sequential enrollment of newborns will follow the inclusion of participants based on eligibility criteria until the sample size is achieved. The inclusion criteria are liveborn infants weighing 500-2499 g with GA information obtained using a qualified last menstrual period or obstetric ultrasound <24 weeks’ gestation (Comparator-GA). Exclusion criteria are structural skin alterations or conditions that modify the skin, such as anhydramnios, hydrops, congenital skin diseases, and chorioamnionitis.

Table 1 illustrates the schedule of enrollment, test application, and endpoint measurement. The skin assessment will occur during the first 24 hours of age. The newborns will be followed up for 72 hours until discharge, held in hospital (for treatment-related purposes), or death, whichever occurs first, considered the study exit. The newborns will continue to receive standard assistance after the study follow-up according to settings, resources, and local staff definitions, whether during hospital admission or at hospital discharge or re-admission.

**Table 1 table1:** Participant timeline of the study.

Study procedures	Before Test-GA	Test-GA, ≤24 hours old	72 hours old: discharged, held in hospital, or death
Enrollment 1: Prospective cohort study^a,b^	X		
Informed consent	X		
Taking of obstetric history	X		
Intervention: Test-GA		X	
Comparator: Best estimation of GA available		X	
Enrollment 2: Nested case–control study^c^			X
Assessments and analysis^d^			X

^a^Inclusion criteria are liveborn, Comparator-GA (reliable last menstrual period [18] or ultrasound assessment at <24 weeks’ gestation [8]), birth weight (500-2499 g), and ≤24 hours old.

^b^Exclusion criteria are malformation with structural skin alterations and skin modifiers (eg, anhydramnios, hydrops, congenital skin diseases, chorioamnionitis).

^c^To determine eligibility criteria for paired allocation according to birth weight range to either the case group (TTN or RDS) or the control group (without TTN, RDS, tachypnea due to other reasons, or bloodstream infection).

^d^Neonatal outcomes including respiratory complications due to prematurity, neonatal intensive care unit admission, or ventilatory support

GA: gestational age; RDS: respiratory distress syndrome; TTN: transitory tachypnea of the newborn.

Within the study cohort, a secondary nested case–control study will include newborns with the following inclusion criteria: (1) for the case group, respiratory distress syndrome or transitory tachypnea of the newborn; (2) for the control group, newborns will be randomly selected with no respiratory diseases or manifestations by other conditions, paired by birth weight range: <1000 g, 1000-1499 g, or 1500-2499 g.

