### Prior Work

The optical properties of the skin’s interaction with light can be evaluated by devices that emit and receive photons [13]. Variations in light scattering through the skin are believed to be associated with changes in skin thickness, the concentration of chromophores, and light wavelength [14]. A novel technology was developed to estimate GA at birth (Test-GA) by analyzing the photobiological properties of the newborn’s skin in combination with clinical variables [15]. This noninvasive and nonionizing technology features a probe containing light emitters and receivers that is brought in contact with the skin over the sole. A mathematical algorithm provides an estimated GA within seconds, combining the skin reflection with clinical adjusters, such as birth weight and incubator stay [15].

The timeline of the new medical device development involves sequential steps [16], represented in Figure 1. The prototype of the device previously evaluated 115 newborns at 24-41 weeks’ gestation with promising results [15]. After insights from this first clinical experiment published in 2017, the technology received improvements to mitigate external influences in the test, such as humidity, ambient light, and to ease the user handling. The current version is a small device, about the size of a pen, with an automated ability to measure skin reflection. To reduce examiner influence, the device now warns about errors of measurement. Clinical variables are presented in a digital screen immediately after the newborn skin assessment. Since February 2019, a clinical trial is taking place in 5 Brazilian hospitals to advance the GA prediction modeling, using a sample of 787 newborns [17]. The planned date of last enrollment is July 2020.

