### Data Definition and Collection

Comparator-GA is calculated by obstetric data obtained at the time of enrollment. The requirements for establishing the best GA calculation (assessed by interviewing the mother) are based on the following:

reliable last menstrual period dating, including certainty about last menstrual dating, regular menstrual cycles, no contraceptives within 3 months of conception, and no abortion or delivery 2 months prior to conception [18]; ORultrasound <24 weeks’ gestation, considered reference for low-income countries as recommended by the World Health Organization (WHO) [8], even if the clinical information on last menstrual period is absent.

For data curation, pregnancy dating based on ultrasonography reports will be adjusted to Intergrowth 21 standards. Fetal crown–rump length [23] as well as femur length and head circumference will be used to recalculate GA [24]. When both ultrasound and reliable last menstrual period dating are available, correction will depend on whether there are discrepancies in excess of 5, 7, 10, or 14 days according to the identified GA at first assessment as recommended in ACOG Committee Opinion guideline number 700 (May 2017) [6].

Test-GA will be determined by statistical analysis according to signals stored in the device’s processor and clinical data. For this, the GA modeling prediction is based on the result of another ongoing clinical trial (registration number RBR-3f5bm5). This study is taking place at 5 Brazilian centers with the analysis of the skin reflection and clinical data of 787 newborns, with 24-42 weeks of gestation, using strict rules of the crown–rump length ultrasound measurement for pregnancy dating [17]. We expect to establish the prediction model toward the end of the RBR-3f5bm5 clinical trial in September 2020.

Birth weight is the first measurement performed by the local staff during the first 24 hours of life. A digital scale for standardizing weighing is already present in all settings.

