### Sample Size

The sample size calculation is estimated based on the primary endpoint. Previous studies reported that Test-GA has 90%-100% accuracy at identifying premature newborns [28]. Using the inferior value of the confidence interval, an overall sample size of 298 newborns, including premature and term, is required for a robust evaluation of the device’s accuracy as recommended by Flahault et al [29].

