### Statistical Analysis

To assess differences between the Test-GA and Comparator-GA estimates, average difference (with standard deviations), intraclass correlation coefficient, paired *t*-testing, and Bland–Altman scatter plots [30] will be used. To evaluate the accuracy of Test-GA in identifying preterm and SGA neonates, sensitivity, specificity (with 95% confidence intervals), and receiver operating characteristic curves and other discriminant analysis techniques will be calculated. The relationship between the measurement of the newborn’s skin reflectance and newborn’s respiratory complications due to immaturity will be evaluated using receiver operating characteristic curves, association tests, and risk ratios. The significance level for hypothesis tests will be 5%, together with 95% confidence intervals.

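### The average difference is pooled over a cohort selected on birth weight, an input of Test-GA, so it can look close to zero while term infants under 2500 g are dated too young

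*Protocol article*

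**What the plan says.** Methods, Eligibility Criteria and Participant Timeline: "The inclusion criteria are liveborn infants weighing 500-2499 g with GA information". The objectives name low-birth-weight newborns as the population of interest, so the weight range is deliberate.

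Introduction, Prior Work, describes the algorithm as "combining the skin reflection with clinical adjusters, such as birth weight and incubator stay". The prototype "previously evaluated 115 newborns at 24-41 weeks" of gestation and was modified afterwards.

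Methods, Data Definition and Collection: the model that produces Test-GA here comes from another trial (RBR-3f5bm5), by "analysis of the skin reflection and clinical data of 787 newborns, with 24-42 weeks of gestation". It is expected in September 2020. No weight limit is stated for that sample or for the prototype sample.

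Methods, Primary Outcomes, names two endpoints: the Test-GA to Comparator-GA difference, and the proportion of preterm newborns correctly detected below 37 weeks with a 1-week margin.

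Methods, Statistical Analysis, begins "To assess differences between the Test-GA and Comparator-GA estimates, average difference (with standard deviations" and goes on to the intraclass correlation, a paired t-test and Bland-Altman plots. No split by preterm or term is stated. Sensitivity and specificity with 95% confidence intervals, and ROC curves, are planned for preterm and SGA status.

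Methods, Sample Size: "Previous studies reported that Test-GA has 90%-100% accuracy at identifying premature newborns". "Using the inferior value of the confidence interval", the article arrives at 298 newborns, preterm and term together, without saying how many of each.

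**The concern.** In a sample without a weight cap most term infants are heavy, so weight helps a model separate term from preterm. In this cohort every term infant weighs under 2500 g, and the weight term pulls each of their estimates down. The larger preterm group can offset this in a pooled mean.

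The study is meant to distinguish preterm infants from small term infants. An average difference near zero with a non-significant t-test would invite the conclusion that Test-GA is unbiased, while the small term infants are systematically dated too young. The same error can reach the SGA endpoint: an under-dated term infant is compared with the standard for a younger gestation, so SGA may be missed.

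The planning accuracy raises a related question. It is attributed to Test-GA, but the model producing Test-GA in this trial did not yet exist.

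**Working it through.** **The plan's own figure.** 298 can be reproduced with an exact binomial calculation, given two inputs that the article does not state: expected accuracy 0.95 (midpoint of 90%-100%) and power 0.95. Require the one-sided 95% lower limit to exceed 0.90:

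- n = 298, at least 277 correct: power 0.954 at a true 0.95; type I error 0.049 at a true 0.90.
- n = 297: power 0.928.

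This is one possible derivation. It gives the number needed for one proportion, whereas the article uses 298 as the overall total.

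**Mechanism.** A fitted model approximates E(GA | weight, skin signal). This expectation holds at every weight, so keeping only weights of 500-2499 g leaves the mean error near zero if the gestational-age mix resembles the model sample's. It does not hold conditional on true GA. With π the term share, b_T the term bias and b_P the preterm bias:

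pooled bias = π × b_T + (1 − π) × b_P

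**Simulation inputs, all assumed.** Mean weight from 650 g at 24 weeks to 3550 g at 42 weeks; weight CV 13% or 16%; skin-signal error SD 1 to 4 weeks; three gestational-age mixes (uniform 24-42 weeks; referral, 35% preterm; general, 10% preterm). The model is cubic in log weight plus skin signal, fitted without a weight cap and applied to 500-2499 g.

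Four settings with weight CV 16% and skin SD 1.5 weeks (bias in weeks):

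| Model mix → cohort mix | π | b_P | b_T | Pooled | Specificity at 37 wk | Specificity at 36 wk |
|---|---|---|---|---|---|---|
| Referral → referral | 0.14 | +0.26 | −1.07 | +0.07 | 0.59 | 0.88 |
| General → general | 0.42 | +0.58 | −0.67 | +0.06 | 0.83 | 0.97 |
| Uniform → general | 0.41 | −0.03 | −1.39 | −0.59 | 0.55 | 0.84 |
| General → referral | 0.14 | +0.57 | −0.55 | +0.41 | 0.78 | 0.96 |

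First row: 0.14 × (−1.07) + 0.86 × 0.26 = −0.150 + 0.224 = +0.07. Third row: 0.41 × (−1.39) + 0.59 × (−0.03) = −0.570 − 0.018 = −0.59. The 36-week column is one reading of the 1-week margin.

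**Ranges over all settings.**

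- Matching mixes: pooled +0.01 to +0.19; term −0.38 to −2.69; preterm +0.03 to +1.07 weeks. Sensitivity 0.93-1.00. Specificity at 37 weeks 0.03-0.88, against 0.86-0.98 without the cap.
- Differing mixes (skin SD 1 to 2.5 weeks): pooled −0.93 to +0.63; term −0.30 to −2.22 weeks.

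**Is it the cap, or ordinary shrinkage?** A separate run, also on assumed inputs, compared the two. Term bias was −0.1 to −0.7 week without the cap and −0.6 to −2.4 weeks with it, while the pooled bias in the capped cohort was 0.01 to 0.06 week. Shrinkage exists without selection; the cap enlarges it.

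**Precision within 298.** The article gives no term share. At an assumed 8%, 298 × 0.08 ≈ 24 term and 274 preterm infants; at 41%, 298 × 0.41 ≈ 122 and 176. For a specificity near 0.90 the exact 95% interval is 0.73-0.99 with 24 term infants and 0.83-0.95 with 122.

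**The case against.** The strongest reply is that nothing in the eligibility rule is wrong. Low-birth-weight newborns are the declared target, and a validation cohort should match its target. This stands: a reader might infer that the cap is a design error, and the documents do not support that.

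Second, the failure would not be hidden. Specificity with confidence intervals, ROC curves and Bland-Altman plots are planned, and SGA accuracy is a secondary analysis. This stands in part. A low specificity would be a warning, but the term group may be small, specificity does not estimate the size of the dating error, and a plot of unlabelled infants does not estimate bias at term.

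Third, a condensed article may leave subgroup tables to an analysis plan. That is fair, and nothing in the article excludes a split. The point rests on what it does state: a primary endpoint summarised by a mean difference and a paired t-test, which followed as written can mislead.

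Fourth, grouping by true GA shows opposite-signed errors even for a calibrated model. This is correct, and it is why the strata should be read together with specificity and not as a pass-or-fail test of bias.

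Fifth, a reader might infer that the 90%-100% figure is wrong, or comes from a sample without a weight cap. The documents do not support either. The figure and the prototype sample carry different citations, and the population behind the figure is not described. Nor does the simulation contradict it as overall accuracy: in a re-run with eight assumed settings, overall accuracy in the 500-2499 g subset was 91%-99%. That agreement is weak reassurance about term infants. In the first table row, with sensitivity 0.99, overall accuracy is 0.86 × 0.99 + 0.14 × 0.59 = 0.93 with a specificity of 0.59.

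**Conclusion.** The concern holds as a weakness in how the first primary endpoint is summarised, not in who is enrolled. Birth weight as a model input, the weight-selected cohort, the model sample described only by gestation and the single average difference are all stated in the article.

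Under-dating of term infants below 2500 g appeared in every setting run, so its direction is robust to the assumptions tried. Its size is not: about −0.3 to −2.7 weeks, depending on weight variation, the strength of the skin signal and the gestational-age mix. It also depends on a model form that is assumed, since the real model was not yet established and incubator stay was left out of the simulation. The specificities depend on how the 1-week margin is applied.

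A reader might infer that the pooled bias will be near zero. The supportable statement is that it can be: this requires a mix like the model sample's, and the article says that validation uses different populations.

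On planning, the accuracy figure cannot come from the model used here, which was expected only in September 2020, and nothing in Sample Size shows that it applies to both preterm and term infants of low birth weight. The split is worth making because it is cheap and addresses the distinction the study exists to draw.

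**What to change.** In Primary Outcomes and Statistical Analysis, add that the Test-GA minus Comparator-GA difference (mean, SD, limits of agreement) will be reported for Comparator-GA below 37 weeks and at or above 37 weeks, and for SGA and non-SGA newborns, alongside the pooled result. State that absence of bias will not be concluded from the pooled mean or its t-test alone, and that the strata will be read with specificity because some shrinkage by true GA occurs even in a calibrated model.

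In Sample Size, state that the 90%-100% figure predates the model used here and that its source population is not described. Restate the expected precision for sensitivity and for specificity separately, at the preterm and term numbers expected within 298. If accuracy is taken from the newborns under 2500 g in RBR-3f5bm5, cross-validate it, because that is the model-building sample and apparent accuracy there is likely to be optimistic.

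Eligibility stays as it is and no new data or participants are needed. The model is due in September 2020, before data collection ends in December 2020. The cost is wider intervals in the small term group and possibly a less favourable planning figure.

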### Study Outcomes

#### Primary Outcomes

The primary endpoints will be differences between the Test-GA and Comparator-GA estimates and proportion of correct preterm newborn detections by the Test-GA at <37 weeks’ gestation with a 1-week margin of error.

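### Siblings from multiple births can be enrolled and would normally share one Comparator-GA and its error, but the named paired t-test assumes independent newborns and no allowance for siblings is shown

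*Protocol article*

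**What the plan says.** - **Who enters (Eligibility Criteria and Participant Timeline).** On recruitment, this section says: "A sequential enrollment of newborns will follow the inclusion of participants based on eligibility criteria until the sample size is achieved". Infants qualify under this rule: "The inclusion criteria are liveborn infants weighing 500-2499 g with GA information obtained using a qualified last menstrual period or obstetric ultrasound" before 24 weeks. The exclusions all concern the skin: "Exclusion criteria are structural skin alterations or conditions that modify the skin, such as anhydramnios, hydrops, congenital skin diseases, and chorioamnionitis". There is no singleton restriction and no limit of one infant per mother. Multiple births are not mentioned anywhere in the article.
- **Where (Study Settings, Ethics, and Dissemination).** Of the hospitals it says: "all of which are referral centers for high-risk pregnancies and neonatal care".
- **Reference standard (Data Definition and Collection).** "Comparator-GA is calculated by obstetric data obtained at the time of enrollment". The sources are the mother's last menstrual period, taken by interview, or an ultrasound before 24 weeks.
- **Endpoints (Primary Outcomes).** "The primary endpoints will be differences between the Test-GA and Comparator-GA estimates and proportion of correct preterm newborn detections". Both use Comparator-GA as the yardstick.
- **Analysis (Statistical Analysis).** For the difference: mean with SD, intraclass correlation between the two methods, a paired t-test and Bland-Altman plots. For accuracy: sensitivity and specificity with 95% intervals, and ROC curves. No clustering term is named.
- **Size (Sample Size).** 298 newborns, with no design effect mentioned.

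**The concern.** Enrolling infants below 2500 g one after another at high-risk referral centres can be expected to bring in some sets of twins, and both infants may qualify. Such a pair adds two newborns to the 298 but normally only one pregnancy dating. Any error in that dating enters both values of Test-GA minus Comparator-GA, and both infants fall in the same preterm or term class.

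The paired t-test pairs two measurements on the same newborn. It does not deal with correlation between two newborns of the same mother. Run on such data, it treats the second twin as fully new information, and so do the usual intervals for proportions. The study is meant to validate the device before it is marketed (Present Protocol of Research), so what is at stake is the stated precision of the agreement and accuracy results.

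**Working it through.** **1. Is an allowance for siblings hidden in 298?** The section gives earlier accuracy of 90%-100% and refers to the lower value. I infer an expected proportion of 0.95 (the midpoint), a lower limit of 0.90, a one-sided 5% level and a 95% probability of success; the article does not state these as a set. The smallest n meeting this under the exact binomial distribution is **298**: at least 277 correct are needed, reached with probability 0.954 if the true value is 0.95. At n = 297 the probability is 0.928. The normal approximation gives 291. Other settings also come close: two-sided 5% with 90% power gives 301 by approximation and 292 exactly. All of these formulas assume independent observations, so on this reading 298 contains no design effect.

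**2. Design effect for the mean difference.** Let f be the share of enrolled newborns whose co-twin is also enrolled, and rho the within-pair correlation of the difference. With n newborns there are nf/2 pairs, so

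Var(mean) = (SD²/n²) × [n + 2 × (nf/2) × rho] = (SD²/n) × (1 + f × rho).

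Hence D = 1 + f × rho. Intervals should be √D times as wide, the effective n is 298/D, and a nominal two-sided 5% test runs at 2 × [1 − Φ(1.96/√D)].

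Neither f nor rho is in the document. I assume f of 10-30% and rho of 0.3-0.7. The middle of the rho range has a simple reading: if dating error and device error had equal variance and only the dating error were shared, rho would be 0.5.

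| f | rho | D | Interval wider by | Effective n | Actual level of a 5% test |
|---|---|---|---|---|---|
| 10% | 0.3 | 1.03 | 1.5% | 289 | 5.35% |
| 20% | 0.5 | 1.10 | 4.9% | 271 | 6.2% |
| 30% | 0.7 | 1.21 | 10% | 246 | 7.5% |
| *Extremes:* 5% | 0.1 | 1.005 | 0.2% | 297 | 5.1% |
| 40% | 1.0 | 1.40 | 18% | 213 | 9.8% |

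**3. Sensitivity and specificity.** These are binary, so rho for the continuous error cannot be used directly. Assume bivariate-normal errors within a pair and 10% misclassified. The correlation of the two right/wrong indicators is then (P(both wrong) − 0.10²)/(0.10 × 0.90).

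- rho = 0.3: (0.0216 − 0.01)/0.09 = 0.13. With f = 10%, D = 1.013, so intervals are 0.6% wider.
- rho = 0.5: (0.0324 − 0.01)/0.09 = 0.25. With f = 20%, D = 1.05, so 2.5% wider.
- rho = 0.7: (0.0468 − 0.01)/0.09 = 0.41. With f = 30%, D = 1.123, so 6% wider.

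For scale, a proportion of 0.90 on all 298 has a half-width of 1.96 × √(0.09/298) = 3.41 points, which becomes 3.41 × 1.0064 = 3.43 to 3.41 × 1.0595 = 3.61 points. Sensitivity and specificity each use only part of the 298, so their half-widths are larger, and f should be read as the share within that part.

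**4. Direction.** For any positive correlation D exceeds 1, so unadjusted intervals are too narrow. The mean difference, sensitivity and specificity themselves are not biased by this. The SD behind the Bland-Altman plot hardly moves either: its expected square falls by a factor of about f × rho/(n − 1), at most 0.21/297 = 0.07% in the assumed band. What would be too narrow is any confidence interval placed around the limits of agreement.

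**The case against.** The strongest reply is that the point rests on silence. The article never says that siblings are treated as independent, and it does not say how the intervals are computed. It is a condensed report, and a variance estimator that respects mothers could sit in an analysis plan that is not shown. Enrolling twins is not a mistake in itself either, for a device intended for low-birth-weight newborns generally.

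Most of this stands, and it limits what may be claimed:

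- A reader might infer that the plan declares all 298 newborns independent. It does not. The inference comes from the named methods, and only infants with an enrolled sibling are affected.
- A reader might put the widening at 5-17% for both primary endpoints. That needs 20-40% of infants in enrolled pairs and correlations of 0.5-0.9, values the document does not supply. Test-GA uses each infant's own skin reflection, birth weight and incubator stay (Prior Work), which can differ between co-twins, so a correlation of 0.9 has no support in the text. Even with those inputs, the figures for the binary endpoint would be about 2.5-12%.
- A reader might infer that no mother identifier is collected. This cannot be checked, because the data entry form (Multimedia Appendix 1) is not shown. Obstetric history is taken and antenatal reports are scanned, so a link may already exist.

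The reply does not remove the point. The article fixes who is enrolled and counted, and it names a test for the first primary endpoint. Run as named on the population admitted, that test understates the standard error whenever enrolled siblings have positively correlated errors.

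**Conclusion.** The point holds as a modest one about precision. Multiple births are admitted by the eligibility rules, co-twins would normally share a dating and its error, and the paired t-test assumes they do not. Under the assumed shares (10-30%) and correlations (0.3-0.7), uncertainty in the mean difference is understated by about 1.5-10% and uncertainty in the accuracy measures by about 0.6-6%. With few enrolled pairs and low correlation the effect is negligible. The direction does not depend on the assumed values as long as the correlation is positive; the size depends on them entirely. The documents do not support a claim that the estimates are biased or that the study's conclusions would change.

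**What to change.** In Statistical Analysis, state that the primary analyses are clustered by mother:

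- mean difference and limits of agreement: a mixed model with a mother effect, or cluster-robust standard errors, in place of the plain paired t-test;
- sensitivity, specificity and area under the ROC curve: GEE, or a bootstrap that resamples mothers;
- sensitivity analysis: repeat the primary analyses with one randomly chosen infant per pregnancy.

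Use the mother link in the obstetric records, after confirming that it is carried into the analysis data set. Report the number of enrolled sibling sets, so that the size of the adjustment can be seen. Eligibility and device procedures stay as they are. The cost is slightly wider intervals and a little more analysis code.

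### The respiratory analysis samples weight-paired controls from a cohort that is already fully measured; using every eligible newborn costs nothing and yields the planned risk ratios directly

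*Protocol article*

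**What the plan says.** Study Design announces the respiratory part as a nested sub-study: "A nested case–control study will evaluate the relationship between the optical properties of the skin and newborn respiratory complications related to prematurity".

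Eligibility Criteria and Participant Timeline gives the sequence for the whole cohort. On the device reading: "The skin assessment will occur during the first 24 hours of age". On follow-up: "The newborns will be followed up for 72 hours until discharge, held in hospital (for treatment-related purposes), or death, whichever occurs first". Table 1 places enrolment into the case–control study in the last column, at 72 hours, after both.

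Pairing appears in two places in that section, worded differently:
- Footnote c of Table 1 gives the purpose of the second enrolment step: "To determine eligibility criteria for paired allocation according to birth weight range to either the case group (TTN or RDS) or the control group". It bars from the control group newborns with TTN, RDS, tachypnea from another cause or bloodstream infection.
- The paragraph after the table defines cases by RDS or TTN alone and attaches the sampling to controls: "for the control group, newborns will be randomly selected". These are paired in three birth weight bands: under 1000 g, 1000–1499 g and 1500–2499 g.

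Statistical Analysis lists ROC curves, association tests and risk ratios for the respiratory outcomes. Sample Size gives one figure, set on the primary endpoint: "an overall sample size of 298 newborns, including premature and term, is required for a robust evaluation of the device’s accuracy".

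**The concern.** A nested case–control sample is worth its loss of information when the exposure is costly to obtain. Here the reading is taken in every newborn before case status is known. To sort newborns into cases and eligible controls, the outcome must also be known for all of them. Sampling therefore buys nothing.

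Three things are at stake for this secondary objective:
- precision, because measured non-cases are set aside;
- the planned risk ratios, because sampling on outcome fixes the proportion of cases;
- the meaning of the AUC, because controls picked to resemble cases in weight are not the low-birth-weight newborns in whom the device would be used.

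**Working it through.** **1. The plan's own figure.** The 298 is for preterm detection, with an expected accuracy of 90% taken from this statement: "Previous studies reported that Test-GA has 90%-100% accuracy at identifying premature newborns". At 0.90 it gives a 95% half-width of 1.96 × √(0.90 × 0.10 / 298) = 0.034. The article gives no lower limit or power, so 298 cannot be re-derived uniquely. Nothing here depends on that; 298 is used as given. No size is stated for the nested study.

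**2. How many newborns are used.** The article gives no control-to-case ratio, no RDS/TTN rate and no distribution over weight bands. All three are assumed:
- ratio 1:1;
- band shares (lowest to highest weight) 10/15/75%, 15/20/65% or 20/25/55%;
- 0, 5 or 10% of each band neither a case nor eligible as a control;
- three sets of RDS/TTN rates, shown in the table.

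Per band, with n = 298 × share, rate r and ineligible share e: cases = n·r; eligible controls = n·(1 − r − e); pairs = the smaller of the two.

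Example with shares 15/20/65%, rates 60/45/20%, e = 0:
- n = 44.7, 59.6, 193.7
- cases = 26.8, 26.8, 38.7 (total 92)
- eligible controls = 17.9, 32.8, 155.0 (total 206)
- pairs = 17.9 + 26.8 + 38.7 = 83.4, so 167 newborns used, 122 eligible controls unused and 9 cases without a partner.

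Ranges over the nine combinations of share and e for each rate set:

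| RDS/TTN rate, lowest to highest band | Cases | Newborns used of 298 | Eligible controls unused | Cases without a 1:1 partner |
|---|---|---|---|---|
| 40/30/10% | 48–63 | 95–125 | 143–203 | 0 |
| 60/45/20% | 83–102 | 148–180 | 82–139 | 6–18 |
| 90/70/30% | 125–155 | 128–167 | 49–89 | 42–91 |

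Eligible controls go unused in every scenario. Unpaired cases do not occur in every one.

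**3. When cases outnumber eligible controls.** This needs r > 1 − r − e, that is r > (1 − e)/2. The threshold is 50% at e = 0, 47.5% at 5%, 45% at 10% and 40% at 20%.

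**4. Precision (Hanley–McNeil, AUC A = 0.80).** Var = [A(1 − A) + (n₁ − 1)(A/(2 − A) − A²) + (n₀ − 1)(2A²/(1 + A) − A²)] / (n₁n₀), with n₁ cases and n₀ controls. The three constants are 0.16, 0.02667 and 0.07111.
- 90 cases, all 208 non-cases: (0.16 + 2.37 + 14.72)/18,720 = 0.000922; SE 0.0304.
- 90 pairs: (0.16 + 2.37 + 6.33)/8,100 = 0.001094; SE 0.0331, which is 9% larger.
- 75 pairs: (0.16 + 1.97 + 5.26)/5,625 = 0.001315; SE 0.0363, which is 19% larger.

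**5. Risk ratios.** Assume two equal groups with risks of 45% and 15%: the true ratio is 3.0 and 30% are cases. Sampling one control per case keeps 0.30/0.70 = 3/7 of the non-cases. The apparent risks become 0.45/(0.45 + 0.55 × 3/7) = 0.656 and 0.15/(0.15 + 0.85 × 3/7) = 0.292, a ratio of 2.25. This is before any weight pairing.

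**6. What the AUC describes.** Prior Work says the gestational age algorithm uses birth weight as an adjuster, and Secondary Outcomes makes Test-GA the respiratory predictor. Pairing on weight removes part of what the predictor carries, so the paired AUC answers a different question from the AUC in the whole cohort.

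**The case against.** The strongest defence is that balancing birth weight is deliberate. Test-GA contains birth weight, so an unadjusted full-cohort AUC could show little more than that lighter babies have more lung disease. That stands, and it is why the fix must keep weight in the analysis. It does not require discarding measured newborns, because a covariate or weight bands do the same job.

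It can also be said that nothing is irrecoverable. Readings are stored and outcomes assessed for everyone, so the full-cohort analysis stays available, and the objective is secondary. That also stands and keeps the point modest.

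Three stronger readings are tempting, and the document does not support them:
- **Unpaired cases are dropped.** A reader might infer this from footnote c. The paragraph after Table 1 defines cases by diagnosis alone and ties pairing to controls, and pairing on three broad bands can be frequency matching, which loses no case. No ratio or discard rule is stated, and none of the listed respiratory analyses needs partners. An article may leave those details to the full protocol, so their absence is not itself criticised.
- **Cases exceed controls below 1500 g.** This depends wholly on assumed rates. At 40/30/10% no band is short. At 60/45/20% only the lowest band is, with 1000–1499 g adequate or at break-even.
- **Pairing doubles the variance.** One simulated scenario gives about that (SE 0.0373 against 0.0267; the squared ratio is 1.95). It is a single set of assumptions and compares two different AUCs. The illustration in the working gives 1.19 to 1.43 times the variance (1.09² and 1.19²).

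**Conclusion.** The point holds as a cheap improvement to a secondary analysis. From the document alone: reading and outcome are on file for the whole cohort before the nested set is formed, so sampling controls saves no measurement; a set sampled on outcome does not give the planned risk ratios directly; and a weight-paired AUC is not the AUC of the low-birth-weight cohort.

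The sizes rest on assumptions. At 1:1, about 95 to 180 of 298 newborns are used. With 90 cases, AUC 0.80 and all 208 non-cases eligible, the standard error is about 9% larger with 90 pairs and 19% larger with 75; the gap narrows slightly if some non-cases are ineligible.

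Loss of cases, which would fall on the bands with the highest rates, remains a conditional risk. It needs both a reading of footnote c as 1:1 pairing with unpaired cases removed, and an RDS/TTN rate above about 45–50% in a band.

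**What to change.** In Eligibility Criteria and Participant Timeline (footnote c and the paragraph after Table 1), replace the sampled, paired controls with all cases and all eligible non-cases in the cohort. In Statistical Analysis, state that birth weight enters as a covariate in a logistic regression, or that the AUC is reported per weight band, or both. Risk ratios can then be taken from the cohort.

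Keep footnote c's exclusion of other tachypnea and bloodstream infection for the main comparison, and add a sensitivity analysis that includes those newborns.

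The cost is a wording change, with no extra newborns or procedures and one step fewer than drawing pairs. The downside is that weight is controlled by a model or by stratification instead of by design. If few unaffected newborns exist in the lowest band, overlap there stays sparse under either approach.
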